### Interventions

#### Eye Movement Desensitization and Reprocessing (EMDR)

EMDR is a psychotherapeutic approach designed to alleviate the distress associated with traumatic memories facilitating the access and process of traumatic memories and other adverse life experience to bring these to an adaptive resolution. The EMDR therapy will consist of 20 individual sessions 60 min each over a period of 6 months. As stated before, the EMDR Bipolar protocol will include an evaluation of the psychiatric history of the patient and an assessment of dysfunctional cognitions and identification of targets in the context of traumatic events. In addition, the reprocessing of traumatic events will follow the standardized protocol of Shapiro [19] together with the five subprotocols specific for BD that target the following areas:
*Mood stabilization*: the major goal in the treatment process of bipolar patients is the long-term normalization of mood. The aim of this protocol is to reinforce the positive experiences of affective stability and self-control in bipolar patients. Via bilateral stimulations this protocol uses also positive cognitions to strengthen the adaptive system of beliefs. When this installation is reinforced repeatedly, patients are expected to experience an improvement in their self-esteem and affective stability that, in turn, is connected with positive body sensations
*Treatment adherence*: poor adherence in bipolar patients is mainly caused by the feeling of being controlled by drugs, (hypo)manic episodes, lack of insight, a negative view on pharmacological treatment, substance abuse, lack of treatment response and side effects such as weight gain and sedation [27]. This protocol aims to identify and improve those issues and strengthen adherence to avoid further affective relapses. First, we find out what subjective problems are connected to the psychopharmacological treatment. Then, the therapist suggests various positive consequences from taking medication. These are then connected to positive cognitions, emotions or body sensations, and installed via bilateral stimulation
*Illness awareness*: the aim is to help clients be more aware of their disease. Good awareness is associated with fewer affective symptoms and risky behavior, better adherence to treatment, and a healthier lifestyle. Being aware of BD can help the client to take medication more reliably, act more consistently concerning eating and sleeping habits, reduce risky behaviors, and facilitates asking for professional help when necessary. In this protocol, the therapist reviews with the patient which kind of affective symptoms suggestive of BD experienced the subject in the past. Then, the therapist proposes positive beliefs connected to the fact of having experienced symptoms and being aware of them; this will be reinforced with bilateral stimulation
*Detection of prodromal symptoms*: the aim of this protocol is to help bipolar patients to identify early prodromal symptoms such as sleep disturbances, mood changes/lability, psychotic symptoms, agitation, restlessness, increased anxiety and changes in appetite or suicidal ideas. In this way, patients can request a rapid therapeutic intervention to avoid an affective relapse. After the identification of individual prodromal symptoms, the therapist proposes a list of positive beliefs connected to the ability to identify prodromal symptoms. Then, the therapist reinforces prodromal symptom awareness with positive cognitions using bilateral stimulation
*De-idealization of pleasurable manic symptoms*: the aim of this protocol is to assist patients who are aware of manic episodes but still idealize specific pleasant euphoric symptoms and ignore the devastating consequences of these symptoms during a manic episode, running a higher risk of poor adherence and further affective relapses. First, the therapist creates with the patient a list of manic-state life experiences that ended in disastrous consequences and connect each experience that occurs during a mixed or manic state with the corresponding impulse, action, sensation, belief and thought. Then, the therapist strengthens via bilateral stimulation the patient’s awareness connecting manic symptoms and impulsivity with disastrous consequences

Some EMDR sessions will be recorded on video randomly and will be evaluated by an external expert in EMDR to verify that the protocol is being administered properly.

#### Individual supportive therapy (ST)

ST is a psychological treatment that encourages patients to express and evaluate their life situation. Living with a mental disease can significantly impact all major domains of life and this can understandably provoke in patients negative feelings such as frustration, helplessness or depressive symptoms. ST also consists of 20 individual sessions of 60 min each over a period of 6 months. One of the main objectives of ST is to offer an opportunity for the subjects to express how their lives are affected by the illness. The ST is a patient-centered, active-listening intervention that enables the patient to receive emotional support and counselling. We also included general advice and information about BD and medication without referring to written or structured material. We offer an unstructured training to enhance assertive behavior; we also include relaxation exercises, problem-solving training and the use of a mood diary or specific mobile app as a tool for tracking the warning signs of a bipolar episode. Single ST was chosen as control condition because it provides an intervention for the patient of similar intensity but with no particular focus on the processing of traumatic events or on structured psychoeducative interventions of the disorder.

### Dropouts and follow-up

In case of an affective relapse with admission to the hospital during the intervention phase of 6 months patients will be excluded from the trial and considered as dropouts. In case of relapse which requires an admission to the hospital during the follow-up, patients will be maintained in the trial to obtain maximum information on the course of the illness.

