### Trial design

This is a single-blind, randomized controlled clinical trial with two parallel branches, EMDR and ST. Patients will be matched for age, sex, illness duration and number of affective episodes the year before the clinical trial. The primary outcome variables that are affective relapses, symptoms of trauma and cognition and psychosocial functioning, will be assessed at six time points; pretreatment (T0), mid-treatment at 2 weeks (T1) and at 3 months (T2), post treatment at 6 months (T3), and follow-up evaluations at 12 (T4) and 24 months (T5) (see Fig. 1). The secondary outcome variables that are the course and prognosis of the disease, will be assessed in follow-up evaluations at 12 (T4) and 24 months (T5). The research assistants conducting the clinical assessments will be blind to the participants’ research condition. Patients are not blind to treatment as it is impossible for a therapist to offer and for a patient to receive therapy without being aware of the techniques that they are using orreceiving. The study has been approved by the Ethics Committee of the Germanes Hospitalàries del Sagrat Cor de Jesús (reference number: PR-2014-15), the Hospital Clínic of Barcelona (reference number: HCB/2015/1005) and the Hospital del Mar (reference number: 2015/6502/l). All participants will sign informed consent prior to enrollment. Details of the trial design can be also gathered from Additional file 1 (Standard Protocol Items: Recommendations for Interventional Trials (SPIRIT) flow diagram) and the SPIRIT Checklist (Additional file 2).

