### Participants

The patient sample will consist of 82 patients fulfilling *Diagnostic and Statistical Manual of Mental Disorders, fourth edition, text revision* (DSM-IV-TR) criteria for bipolar I and II disorder, based on clinical interview and review of case notes. Inclusion criteria will be: (1) age between 18 and 65 years, (2) presence of between two and six affective episodes in the last year, (3) current clinical status of euthymia upon clinical evaluation, defined as the presence of clinical remission (Bipolar Depression Rating Scale (BDRS) <8 and Young Mania Rating Scale (YMRS) <6; or subsyndromal status defined as BDRS ≥8 and <14 and/or YMRS ≥7 and <12), (4) presence of one or more traumatic events causing current trauma-related symptoms (The Holmes-Rahe Life Stress Inventory, H-RLSI >0; The Clinician-administered PTSD Scale (CAPS): frequency event >1, intensity of symptom >2; Impact of Event Scale-Revised, IES-R >0), and – following the standard EMDR protocol [19] – Subjective Units of Distress (SUD) >5 (range from 0 to 10, with a score of 10 meaning maximum stress).

Exclusion criteria will be: (1) substance abuse/dependency within 3 months prior to participation (except of nicotine abuse/dependency), (2) neurological disease or brain trauma history, (3) suicidal ideation, (4) previous involvement in trauma-focused therapy, (5) current psychotherapy during the study and months of follow-up.

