### Computation of sample size

The main aim of the study is to assess the relative efficacy of a specific EMDR intervention protocol versus ST therapy in the clinical stabilization (decrease in the risk of relapse) of traumatized bipolar patients. For this reason the reduction of the risk of relapse after treatment with a follow-up of 24 months will be used as the dependent variable of the study. The calculation of the sample size was based on a survival analysis using the statistical package “powerSurvEpi” for R (http://www.r-project.org/) using an alpha = 0.005 instead of 0.05 to allow correction for multiple comparisons. The number of patients required to detect a hazard ratio = 2 (i.e., the hazard rate of relapse is one group is the double of the hazard rate in the other group) in a Cox regression with a statistical power of 80% and alpha = 0.005 is *n* = 36 per intervention group (two groups, EMDR and ST, equals to a total *n* = 72). According to Chambless and Hollon (1998) a sample of this size should show clinically relevant differences [27]. Assuming a percentage of dropouts of about 10–15% of the participants it would be necessary to recruit approximately 82 patients, 41 allocated in each intervention arm.

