## Statistical analysis

The baseline distribution of sociodemographic and clinical characteristics in each treatment arm will be reported using descriptive statistics.

The main hypothesis of the change in the time to relapse (in weeks) will be analyzed using Cox regressions, and the hypotheses of the changes in the scores of clinical scales as compared to baseline will be tested using repeated measures analyses of variance (ANOVAs) that will include time, treatment arm and their interaction. Those variables that show statistically significant between-arm differences at baseline will be added as covariates in the Cox regressions and repeated measures ANOVAs. For each of the analyses effect size measures (hazard ratio or Hedges’ *g*) will be estimated.

An intention-to-treat (ITT) analysis will be employed to provide unbiased comparisons among the treatment groups, using multiple imputations to deal with the losses of follow-up.

R software will be used to carry out the statistical analyses.

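### Patients admitted for an affective relapse during the 6-month intervention leave the trial as dropouts, an outcome-triggered removal that conflicts with the promised ITT analysis of relapse

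*Protocol article*

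**What the plan says.** All references are to the Protocol article.

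- **Dropouts and follow-up.** For an affective relapse with admission to hospital: "during the intervention phase of 6 months patients will be excluded from the trial and considered as dropouts". For the same event in the follow-up period: "patients will be maintained in the trial to obtain maximum information on the course of the illness".
- **Primary outcome.** The Abstract names fewer affective episodes after 12 and 24 months. Trial design lists, as primary outcome variables, "affective relapses, symptoms of trauma and cognition and psychosocial functioning, will be assessed at six time points", running from baseline (T0) to 24 months (T5).
- **Primary analysis.** Statistical analysis: "The main hypothesis of the change in the time to relapse (in weeks) will be analyzed using Cox regressions".
- **Start of the clock.** Computation of sample size: "reduction of the risk of relapse after treatment with a follow-up of 24 months will be used as the dependent variable".
- **Analysis set and missing data.** Statistical analysis: "An intention-to-treat (ITT) analysis will be employed to provide unbiased comparisons among the treatment groups". Multiple imputation is to handle losses to follow-up.
- **Assessments.** Tables 1-3 schedule symptom, trauma, cognition and functioning measures at T3, T4 and T5 (6, 12 and 24 months).

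The article does not say whether the admission that triggers exclusion is entered as a relapse in the Cox regression.

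**The concern.** Relapse is what the trial sets out to prevent, and a relapse severe enough to need admission is also the trigger for exclusion. Membership of the followed-up population therefore depends on a post-randomisation event that treatment may affect. The same event after month 6 has the opposite consequence.

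Two kinds of information are at stake:

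- **The relapse itself.** If the patient is handled as a dropout, a dated event may enter the Cox regression as a censored time or not at all.
- **Everything after it.** Exclusion from the trial ends the T3-T5 assessments for patients with a poor early course. Multiple imputation is a weak repair. Every patient with an early admitted relapse leaves, so nobody with that history has later data from which an imputation model could learn.

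If early admission is equally common among relapses in both arms, the cost is mainly power. If it differs by arm, the estimated hazard ratio is biased.

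**Working it through.** **1. The plan's own figures.** The stated requirement is 36 per group (72), from a hazard ratio of 2, 80% power and alpha 0.005, raised to 82 for 10-15% dropout.

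- The inflation is consistent: 72/(1 − 0.12) = 81.8, about 82. The allowance is 82 − 72 = 10 patients.
- The 72 is not reproduced at alpha 0.005. Schoenfeld's formula, two-sided, gives 4 × (2.807 + 0.842)² / (ln 2)² = 111 events, or 56 per arm even if everyone relapses.
- The stated 36 appears with Freedman's formula at two-sided alpha 0.05 and 100% relapse: (1.960 + 0.842)² × 3² = 70.6, so 71 events, and 70.6/2 = 35.3, rounded up to 36.

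This is a separate matter. It is noted only because it explains why the starting power below is well under 80% at alpha 0.005.

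**2. Inputs for the check.** From the documents: 41 per arm, hazard ratio 2, 24 months, a 6-month intervention, alpha 0.005 (0.05 also shown; two-sided assumed, as sidedness is not stated). The Background gives almost 70% relapse within 2 to 4 years. Entry requires two to six episodes in the last year, so a higher risk is plausible. Assumed: relapse by 24 months under supportive therapy (ST) of 70% or 90%; exponential relapse times; 20-50% of relapses before month 6 admitted.

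**3. Expected removals, equal admission shares.** Monthly ST hazard λ = −ln(1 − p)/24; EMDR hazard λ/2. Removed per arm = 41 × share × (1 − e^(−6 × hazard)).

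- p = 70%: λ = 0.0502. Relapse before month 6 is 26.0% (ST) and 14.0% (EMDR). At a 30% share, 3.2 + 1.7 = 4.9 patients; at 50%, 5.3 + 2.9 = 8.2.
- p = 90%: λ = 0.0959. Relapse before month 6 is 43.8% and 25.0%. At 30%, 5.4 + 3.1 = 8.5; at 50%, 9.0 + 5.1 = 14.1.

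So about 5 to 14 of 82 patients (6-17%) are removed, against an allowance of 10 for all dropout.

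**4. Effect on the Cox regression.** Simulation, 2,000 trials per scenario, one-covariate Cox model. Each arrow runs from counting the early admitted relapse as an event to censoring it as a dropout. The hazard ratio (HR) is ST relative to EMDR.

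| ST relapse | Share admitted, EMDR / ST | Removed, EMDR + ST | HR | Power, alpha 0.05 | Power, alpha 0.005 |
|---|---|---|---|---|---|
| 70% | 30% / 30% | 1.8 + 3.2 | 2.02 → 2.03 | 0.66 → 0.61 | 0.30 → 0.26 |
| 70% | 50% / 50% | 2.9 + 5.4 | 2.02 → 2.02 | 0.64 → 0.56 | 0.30 → 0.24 |
| 90% | 30% / 30% | 3.1 + 5.5 | 2.02 → 2.01 | 0.79 → 0.73 | 0.47 → 0.40 |
| 90% | 50% / 50% | 5.2 + 8.9 | 2.00 → 2.01 | 0.79 → 0.69 | 0.45 → 0.33 |
| 70% | 20% / 50% | 1.2 + 5.3 | 2.01 → 1.80 | 0.65 → 0.44 | 0.29 → 0.15 |
| 90% | 20% / 50% | 2.1 + 9.0 | 2.00 → 1.72 | 0.78 → 0.49 | 0.46 → 0.19 |
| 70% | 50% / 20% | 2.9 + 2.1 | 2.05 → 2.31 | 0.67 → 0.76 | 0.31 → 0.39 |
| 90% | 50% / 20% | 5.2 + 3.6 | 2.01 → 2.34 | 0.79 → 0.88 | 0.46 → 0.59 |

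Deleting the patients instead of censoring them gives nearly the same hazard ratios: 1.78-1.82 and 2.30-2.32 in the unequal cases. The simulation censors or deletes; it does not imputate event times.

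**5. Start of the clock.** Trial design has relapse assessed from T0, while the sample-size section speaks of relapse after treatment. If time zero is month 6, the early admissions are not primary events. The comparison is then between those in each arm who completed six months without an admitted relapse, which is still selection after randomisation on something treatment can affect.

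**The case against.** The strongest reply is that calling these patients dropouts does not say that their relapse goes uncounted. The admission date is known when the patient is excluded, so time to first relapse can be analysed in all randomised patients with the admission as an event. That stands. A reader might infer that an ITT analysis is impossible, but the documents do not support that. The problem is that the rule, followed as written, does not deliver one. Nor can an analysis plan recover T3-T5 data that are never collected.

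Other stronger readings are tempting and should not be adopted:

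- **That known relapses will be overwritten by imputed values.** Imputation is stated for losses to follow-up. Its use over an observed relapse would be an inference.
- **That the hazard ratio is necessarily biased.** With equal admission shares it is not.
- **That exclusion criterion 5 has the same defect.** It covers "current psychotherapy during the study and months of follow-up", but stands among the eligibility criteria, and no rule says that patients who start psychotherapy later are removed.
- **That the main safety signal is hidden.** Nothing prevents dropouts being reported by arm and reason, and the article does not identify early admissions as the main safety signal.

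It is also fair to say that the size rests on unsourced admission shares. At 70% relapse, removals are about 5-8 of 82, which does not exhaust the dropout allowance.

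**Conclusion.** The concern holds as a conflict between two stated rules. Removal triggered by the primary outcome, applied in months 0-6 but not afterwards, cannot be squared as written with an ITT analysis intended "to provide unbiased comparisons among the treatment groups". The unclear time origin adds to the conflict but does not remove it.

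With 41 per arm, a true hazard ratio of 2, and 70-90% relapse by 24 months under supportive therapy:

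- **Equal admission shares (30-50% of early relapses):** about 5-14 of 82 patients are lost and the hazard ratio is unbiased. At alpha 0.005, power falls from about 0.30 to 0.24-0.26 (70% relapse) or from about 0.46 to 0.33-0.40 (90%). At alpha 0.05, it falls from about 0.65 to 0.56-0.61 or from about 0.79 to 0.69-0.73.
- **Unequal shares (20% against 50%):** the hazard ratio moves to about 1.7-1.8 or about 2.3. The direction depends on which arm has the larger share.

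These figures apply if the admission is censored or the patient deleted. If it is counted as an event from randomisation, the loss for time to first relapse disappears, but the missing T3-T5 data remain. The change is needed while patients are still under observation, because lost follow-up cannot be rebuilt later.

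**What to change.** Amend the protocol so that Trial design, Computation of sample size, Dropouts and follow-up, and Statistical analysis agree:

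1. Separate stopping sessions from leaving the trial. Whether sessions continue after an admission is a clinical decision and is not addressed here.
2. State that time zero is randomisation, and that any relapse from then on, including one with admission in months 0-6, is a primary event at its date.
3. Continue the scheduled outcome assessments for these patients and analyse all randomised patients in their allocated arm.
4. Reserve censoring or imputation for true loss to follow-up, and never impute over an observed relapse.
5. Report early admissions by arm.

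The cost is one amendment, matching analysis wording, and visits already in the schedule for roughly 5-14 patients under the assumptions above. Trial status says recruitment began in July 2016, so some patients may already have been excluded and would need to be recontacted.

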### Assessments

Demographical and clinical variables will be collected through an interview using the medical history of the patients and a specific Case Report Form (CRF) for the study, including sex, age, age of onset of the disorder, number of relapses, number of previous episodes, history and number of suicide attempts previous and current pharmacological treatment, family background and consumption of drugs. To ensure privacy of participants and safe data storage, data will also be entered in a data file anonymously; participants will be given a unique number, and only the research assistant will be able to link the number with the name of the patient. At baseline (T0) research assistants will also assess clinical severity of affective symptoms, presence of traumatic live events and trauma symptoms, and cognitive and psychosocial functioning. At 2 weeks (T1) and 3 months (T2) of treatment patients will be evaluated with respect to clinical symptoms. After the treatment phase (T3) subjects will be interviewed with respect to clinical symptoms, trauma scales, cognitive and psychosocial functioning and patient satisfaction. During two follow-up visits at 1 year (T4) and 2 years (T5), blind-to-treatment evaluators apply clinical affective and trauma scales, functioning and cognition. See Fig. 1 (flow diagram of enrollment, intervention and assessments).

The clinical severity will be assessed by means of different instruments (see Table 1):

**Table 1 Tab1:** Measurements to evaluate clinical variables

Clinical variable	Measurement interview/Self-report	T0	T1	T2	T3	T4	T5
		Baseline	Mid-treatment		Post treatment	FU 12 months	FU 24 months
Mania	Young	x	x	x	X	x	x
Depression	BDRS	x	x	x	X	x	x
Severity	CGI-BP-M	x	x	x	X	x	x

*FU* Follow-up, *YMRS* Young Mania Rating Scale, *BDRS* Bipolar Depression Rating Scale, *CGI-BP-M* Clinical Global Impression Scale modified for bipolar disorder

The BDRS [28], Spanish validation (BDRS-S) [29]: the BDRS is the most up-to-date and appropriate tool to assess depressive and mixed symptoms in DSM-IV-diagnosed bipolar I and II patients. The BDRS comprises 20 items that evaluate the clinical features associated with the depressive phase of BD, including atypical symptoms and mixed phenomenology [28]. Symptom severity are rate on a 4-point scale ranging from 0 = no symptoms present, 1 = mild, 2 = moderate, 3 = severeThe YMRS [30], Spanish validation [31], is a heteroadministered scale composed of 11 items aimed at quantifying the severity of manic and hypomanic episodes. There are four items that are graded on a 0 to 8 scale (irritability, speech, thought content and disruptive/aggressive behavior), while the remaining seven items are graded on a 0 to 4 scale. These four items are given twice the weight of the others to compensate for poor cooperation from severely ill patients. Strengths of the YMRS include its brevity, widely accepted use, and ease of administrationThe Clinical Global Impression Scale modified for BD (CGI-BP-M) [32], Spanish validation [33]: the CGI-BP-M scale consists of three subscales; the first two assess the severity of acute symptoms of mania and depression, and the third evaluates the longitudinal severity of the disease. Each subscale has seven subcategories with scores from 1 to 7 rating the severity of the disorder as normal, low, mild, moderate, marked, severe or very severe

Trauma symptoms will be evaluated using the tools listed in Table 2:

**Table 2 Tab2:** Measurements to evaluate trauma symptoms

Clinical variable	Measurement interview/Self-report	T0	T1	T2	T3	T4	T5
		Baseline	Mid-treatment		Post treatment	FU 12 months	FU 24 months
PTSD	CAPS	x			x	x	x
Adverse events	IES-R	x			x	x	x
	H-RLSI	x					
	SUD	x			x	x	x

*FU* Follow-up, *PTSD* Posttraumatic Stress Disorder, *CAPS* The Clinician-administered PTSD Scale, *IES-R* Impact Event Scale, *H-RLSI* The Holmes-Rahe Life Stress Inventory, *SUD* Subjective Units of Distress

The Clinician-Administered PTSD Scale (CAPS) [34], Spanish validation [35]: the CAPS is the standard scale in the evaluation of the presence or absence of PTSD diagnosis and the frequency and intensity of the symptoms. This scale provides ratings of the frequency and intensity of each of the 17 DSM-IV-TR-based PTSD symptoms on a 0 to 4 Likert-type scale, thereby allowing for a maximal score of 8 for each symptom and a total score range from 0 to 136 [23]. It can be used to diagnose a current or past trauma, or to evaluate symptoms during the last weekThe Impact of Event Scale Revised (IES-R) [36], Spanish validation [37]: the IES-R is a 22-item self-report measure that assesses subjective distress caused by traumatic events. Items correspond directly to 14 of the 17 DSM-IV symptoms of PTSD. Patients are asked to identify a specific stressful life event and then indicate how much they were distressed or bothered during the past 7 days. Items are rated on a 5-point scale ranging from 0 = not at all, 1 = a little bit, 2 = moderately, 3 = quite a bit and 4 = extremely. The IES-R yields a total score (ranging from 0 to 88) and subscale scores can also be calculated for the Intrusion, Avoidance and Hyperarousal subscalesThe Holmes-Rahe Life Stress Inventory [38], Spanish validation [39]. This scale assesses frequency of 43 common stressful life events that occurred over the previous 12 months, providing a standardized measure of the impact of these stressors [40]. Interpretation of the overall score is difficult because of the large differences in each person’s ability to cope and their particular reactions to stress, but there are some general guidelines. Scores below 150 reflect low levels of stress, scores between 150 and 299 represent a 50% risk of illness in the near future and scores above 300 represent an 80% risk of developing a stress-related illness [38]

Cognitive profiles and overall functioning will be evaluated using (see Table 3):

**Table 3 Tab3:** Measurements to evaluate cognitive and functional profiles and satisfaction with the treatment

Clinical variable	Measurement interview/Self-report	T0	T1	T2	T3	T4	T5
		Baseline	Mid-treatment		Post treatment	FU 12 months	FU 24 months
Cognition	SCIP	x			x	x	x
	MSCEIT	x			x	x	x
Functionality	FAST	x			x	x	x
Satisfaction	CLQ-8				x		

*FU* Follow-up, *SCIP* Screen for Cognitive Impairment in Psychiatry, *MSCEIT* The Mayer-Salovey-Caruso Emotional Intelligence Test, *FAST* Functioning Assessment Short Test, *CLQ-8* Client Satisfaction Questionnaire

Screen for Cognitive Impairment in Psychiatry (SCIP) [41], Spanish validation [42]: the SCIP is a short tool to assess cognitive impairment in psychiatric patients and consists of five subtests that assess immediate and delayed verbal learning, working memory, verbal language, and processing speed. Three alternate forms facilitate their application to assess possible cognitive changes and avoid habituation and learning effects in repetitive within-patient evaluations. The SCIP-S yields a total score and subscale scores can also be calculated for every single cognitive function evaluatedThe Mayer-Salovey-Caruso Emotional Intelligence Test (MSCEIT) [43], Spanish validation [44]. The MSCEIT evaluates emotional intelligence based on scenarios typical of everyday life. This test measures how well people perform tasks and solve emotional problems, rather than having them provide their own subjective assessment of their emotional skills [43]. The MSCEIT consists of 141 items and the results are presented in a comprehensive personal summary report providing graphical representations of 15 separate emotional intelligence scores and a detailed explanation of score meanings. The MSCEIT provides a total score, two general areas of emotional intelligence (experiential and strategic), four branches of emotional intelligence (perceiving emotions, using emotions, understanding emotions and managing emotions) and eight specific emotional intelligence tasks (identifying emotions in pictures and in faces, relating emotions to sensation and to thinking, analyzing complex emotions and chains of emotions, and incorporating into decision-making your own emotions and the emotions of others)Functioning Assessment Short Test (FAST) [45]: the FAST is a brief instrument to evaluate performance in six different areas of functioning, such as autonomy, occupational functioning, cognitive functioning, finances, relationships and leisure. This test contains 24 items and all of them are rated on a 4-point scale. The global score is obtained by summing the scores of each item (ranging from 0 to 72); higher scores indicate poorer functional status

Finally, to measure patient satisfaction with the treatment, we will use the Client Satisfaction Questionnaire (CSQ-8) [46], Spanish validation [47]. The CSQ-8 is an eight-item, easily scored and administered measurement that is designed to measure client satisfaction with services. The items for the CSQ-8 were selected on the basis of ratings by mental health professionals of a number of items that could be related to client satisfaction and by subsequent factor analysis. The CSQ-8 is unidimensional, yielding a homogeneous estimate of general satisfaction with services. The CSQ-8 provides a total score (ranging from 8 to 32), with high scores indicating greater satisfaction.

